**7.2 Analyses based on individual pupil’s outcome**

*Marginal models:*

The marginal probabilty of unprotected intercourse by age 16 and of termination of pregnancy by age 19 will be compared between the intervention and control schools using the Generalized Estimating Equations approach of Liang and Zeger. [22]

*Conditional Models:*

The probability of outcome conditional on school effect will be compared between the intervention and control arms by fitting multilevel methods with random effects for school and cohort using MLwin.

Secondary analyses will adjust the comparisons using marginal models and conditional models for pupil level covariates: sex (first primary endpoint only), ethnic origin, social class etc.

- 1. **Analysis of process data**

Data collected from focus group discussions with students and peer educators, interviews with teachers, observation of lessons and researcher field diaries are transcribed and analysed using a variety of approaches including thematic content analysis and discourse analysis. A particular challenge is to move beyond the usual practice in which 'qualitative' data are analysed separately and sit alongside 'quantitative' measures of outcome. To integrate process and outcome evaluations, qualitative process data are coded to create variables which describe the implementation and acceptability of the intervention. Data on these variables are entered into the computer database and analysed with the data from questionnaire surveys. Data from the process evaluation may also be analysed independently of the data from the questionnaire surveys to generate hypotheses about the importance and impact of local effects on outcomes in individual or groups of schools. The data will also be analysed to address other important questions, for example to describe the type of young people who volunteer to be peer educators and the impact on them of their involvement in the programme.

8 Trial Steering Committee

The trial has a steering committee whose members are:

[name] (Chair), LSHTM

[name], Head of Watford Grammar School

[name], Health Education Co-ordinator, Camden Education Department

[name], R&D Division, Department of Health

[name], MRC Sociology Unit

MRC Observer.

The steering committee provides advice to the research team, and ensures that the trial is conducted to the standards set out in the MRC Guidelines for Good Clinical Practice. In particular, the steering committee is asked to concentrate on progress of the trial, adherence to the protocol, participant safety and consideration of new information. It meets approximately twice a year and provides an annual report to the MRC on the progress of the trial. At each meeting, the research team presents at least as much information about the status / progress of the trial as the steering committee needs to make its report. These meetings also provide an opportunity for members of the research team and steering committee to discuss and anticipate potential problems including relations with the media. An independent data-monitoring committee was considered unnecessary by the MRC.

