##### Trial endpoints

**Phase 1**: Primary endpoints are unprotected sexual intercourse before the age of 16 and regretted sexual relationships. Other phase 1 endpoints relate to the Government’s Teenage Pregnancy Strategy,[3] including pupil satisfaction with school sex education, ability to access sexual health services, condom use at first and last intercourse and appropriate use of contraception. In terms of secondary objectives, the process evaluation will identify reasons for continuing, extending or changing the method of sex education used during the study, and assess staff attitudes to future provision of sex education.

**Phase II**: Primary endpoint is cumulative incidence of termination of pregnancy by age 19-20. The Chief Medical Officer has agreed to the use of statutory abortion notifications for this purpose. Anonymised data will be obtained from the Office of National Statistics on abortions in both experimental and control schools. This means that there will be no loss to follow-up for the primary outcome. In addition to unprotected intercourse and regretted sexual relationships, phase II outcomes will include markers of exposure to STI i.e chlamydia and herpes genital infections through measurement of type specific *C. trachomatis* and Herpes simplex virus 2 antibodies respectively.

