**4.4 Sample size and power calculations**:

The power calculation takes into account that the school, not the individual, is the unit of randomisation. [20] The number of schools required for the trial depends on 1) the expected incidence rate of the main outcome in the absence of any intervention 2) the variability in the incidence rate between schools 3) the number of participating pupils in each school 4) the magnitude of effect of the intervention that the trial is intended to detect and 5) the desired degree of certainty (statistical power) with which such an effect is to be detected. Termination of pregnancy was chosen as the primary outcome on which to estimate the size of the trial because it is an important and relatively uncommon event for which reliable data are available. Based on the legal abortion rate for 16-19 year olds in England and Wales in 1994 (23 per 1000), the expected cumulative incidence of termination by age 20 will be at least 9%. The variability in outcome between schools can be expressed as k (the coefficient of variation (SD/Mean) of the incidence rate) which, in the absence of reliable data, was assumed to be 0.2. The same variability can also be expressed as a standard deviation of 1.8% which translates into nearly 3 fold variation between schools in the abortion rate from 5% to 13%. With these assumptions, 14 schools, with an average of 150 girls in each, would be needed in each arm to detect a one third reduction in the termination rate, from 9% in control schools to 6% in intervention schools, with over 80% statistical power at 5% significance. However, the value of k, or the extent of between school variability can be reduced by effective stratification of schools (see 4.5 below), thus making the sample size estimates conservative.

The trial will have over 90% power to detect a reduction in the proportion of pupils having unprotected intercourse before age 16, from 35% to 25%, assuming a standard deviation of 8.2% which gives a range of 19% to 51% between schools. Two successive cohorts of Year 9 pupils (with average Year size 150 pupils, or 75 girls) are recruited in each school to provide adequate statistical power. Total number of participants is over 8000.

**4.5 Method of randomisation**.

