### Plan of analysis

For each of the two primary end points (unprotected sexual intercourse before the age of 16 and termination of pregnancy), the following analyses will be undertaken:

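### Termination of pregnancy is sized to age 20, defined at 19-20 and analysed at 19; if the last is read strictly, power is about 75% rather than over 80%

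*Protocol*

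**What the plan says.** The protocol fixes, or leaves open, the age limit for termination of pregnancy in four places.

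- **Section 4.4, Sample size and power calculations:** "the expected cumulative incidence of termination by age 20 will be at least 9" per cent. The source is given as "Based on the legal abortion rate for 16-19 year olds in England and Wales in 1994 (23 per 1000" women per year). On this basis "14 schools, with an average of 150 girls in each, would be needed in each arm" to detect a fall from 9% to 6% with over 80% power at the 5% level. The between-school coefficient of variation is k, "which, in the absence of reliable data, was assumed to be 0.2".
- **Trial endpoints, Phase II:** "Primary endpoint is cumulative incidence of termination of pregnancy by age 19-20".
- **Section 7.2, marginal models:** the marginal probability "of termination of pregnancy by age 19 will be compared between the intervention and control schools". The sentence on conditional models gives no age.
- **Section 7.1, school-level analyses:** average annual rates per person-year are compared, with no age at which the person-years end.

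Table II places the linkage to routine data on conceptions and abortions in Summer 2005.

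**The concern.** Termination is the outcome on which the number of schools was chosen. Its events accrue with age, so the age limit decides how many events enter the comparison. The 9% needs all four years from the 16th to the 20th birthday. An analysis that stops at the 19th birthday uses three of them.

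Two things are at stake. First, the margin in the sample size is thin, just under one school per arm, so losing a quarter of the planned observation time could use it up. Second, with several limits on the page and none declared to govern, the limit could be settled after the linked data have been seen.

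**Working it through.** **Step 1. What by age 19 means.** The same sentence in section 7.2 puts the other primary endpoint, unprotected intercourse, at by age 16. The opening of the Plan of analysis names that endpoint as "unprotected sexual intercourse before the age of 16 and termination of pregnancy" names the second. So in this sentence by age 16 stands for before the 16th birthday, and by age 19 read alike means before the 19th birthday. Section 4.4 uses by age 20 in the same way: 4 years × 2.3% = 9.2%, which matches at least 9%.

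**Step 2. Inputs.** From section 4.4: c = 14 schools per arm, m = 150 girls per school, k = 0.2, one-third reduction, 5% significance. I take the test as two-sided, which the protocol does not state. The protocol does not print its formula. I use the usual one for unmatched cluster trials based on k:

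V = [p0(1 − p0) + p1(1 − p1)]/m + k²(p0² + p1²)

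schools per arm for 80% power = 1 + (1.96 + 0.8416)² × V/(p0 − p1)²

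power at c schools = Φ{√[(c − 1)(p0 − p1)²/V] − 1.96}

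**Step 3. Reproduce the stated design (9% against 6%).**

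- V = (0.0819 + 0.0564)/150 + 0.04 × (0.0081 + 0.0036) = 0.000922 + 0.000468 = 0.001390
- Schools per arm = 1 + 7.849 × 0.001390/0.0009 = 13.1
- Power at 14 = Φ(2.901 − 1.96) = 82.7%

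This agrees with the protocol's 14 schools and over 80%.

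**Step 4. Three years instead of four.** With a flat annual rate, control incidence is 3 × 2.3% = 6.9%, and two thirds of that is 4.6%.

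- V = (0.06424 + 0.04388)/150 + 0.04 × (0.004761 + 0.002116) = 0.000721 + 0.000275 = 0.000996
- Schools per arm = 1 + 7.849 × 0.000996/0.000529 = 15.8, so 16
- Power at 14 = Φ(2.628 − 1.96) = 74.8%

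**Step 5. Dependence on method (k = 0.2).**

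| Method | Four years | Three years |
| --- | --- | --- |
| Formula above | 82.7% | 74.8% |
| Without the extra school | 85.3% | 77.9% |
| Noncentral t, 26 df | 82.6% | 74.7% |
| Person-years version | 81.2% | 72.9% |

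Each of these variants exceeds 80% at four years and falls below it at three. Taking three quarters of 9% (6.75%) instead of 6.9% gives 74.1%. Holding the between-school SD at 1.8% in both arms gives 77.9% and 61.1%; it does not reproduce the protocol's figure, so I set it aside.

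**Step 6. Dependence on k.**

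| k | 9% against 6% | 6.9% against 4.6% |
| --- | --- | --- |
| 0.10 | 91.9% | 83.9% |
| 0.15 | 88.1% | 80.0% |
| 0.20 | 82.7% | 74.8% |
| 0.25 | 75.8% | 68.6% |

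**Step 7. Can the data reach age 20?** Cohort 2 is in Year 9 (ages 13-14) in 1998/99. If its members turn 14 by the end of summer 1999, the youngest turn 20 by the end of summer 2005, since 1999 + 6 = 2005. Cohort 1 is a year older. Linkage is planned for Summer 2005, so the planned data cover almost all of the sized window, and an age-19 limit would discard events that the trial collects.

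**The case against.** A reader might infer that the trial is underpowered, or that its sample size calculation is wrong. The documents do not support that. The calculation reproduces, and follow-up to 19-20, the endpoint definition and the linkage date all point to about age 20. The likeliest explanation is one stray age in section 7.2. That phrase could also be a loose way of saying through age 19, since the planning rate is for 16-19 year olds, and then no power is lost. This stands as a limit on the size of the problem. It does not remove the conflict, and the strict reading has the better textual support.

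The loss is also confined. The age 19 limit appears only in the marginal-model sentence. The analysis that uses k is the school-level one in section 7.1, which carries no limit. That is fair, but it means section 7.1 needs an age limit as well.

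The 6.9% is my derivation, not a protocol figure. It assumes a flat rate between 16 and 19 and leaves out terminations before 16, as the arithmetic behind the 9% also does. Section 4.4 says at least 9% and expects stratification to lower k, and at k = 0.15 the three-year power is 80.0%. But the protocol takes no numerical credit for this, and k was assumed without reliable data.

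A reader might finally infer a further loss of power from imperfect linkage, given the statement "This means that there will be no loss to follow-up for the primary outcome". The documents give no matching method, match rate or out-migration figure, so any such loss would rest on invented capture rates. I do not make that point.

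**Conclusion.** The inconsistency is real: the outcome that sized the trial has limits of 20, 19-20 and 19, plus one analysis with none. As section 7.2 is most naturally read, the marginal-model comparison stops a year short of the window behind the 9%. Its power is then about 75% rather than over 80%, and about 16 schools per arm would be needed for 80%.

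That size is conditional on the strict reading, a flat annual rate of 23 per 1000, a one-third reduction and k = 0.2. Under the loose reading the power loss is nil, and at k = 0.15 power is still about 80%. What does not depend on these assumptions is that the protocol must name one age limit before the linked data are analysed.

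**What to change.** State one limit, termination before the 20th birthday, in four places: the Phase II endpoint definition, section 4.4, section 7.1 (as the end of person-years) and section 7.2 (for both the marginal and the conditional models). Set the linkage extraction so that the youngest cohort 2 girls have reached 20, about the end of summer 2005.

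If age 19 is really intended, use that limit in all four places instead. Restate the planning incidence as about 6.9% and the power as about 75%, with the assumptions of k = 0.2 and a flat annual rate written beside them.

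The cost is a few wording changes and possibly a slightly later extraction. Under the second option it is also a less favourable stated power.

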**3. Aims and objectives**

The aim of the trial is to evaluate the effectiveness of school-based peer-led sex education in promoting young people’s sexual health

The primary objective is to measure the effectiveness of peer-led sex education in reducing the incidence of unwanted pregnancy, termination of pregnancy, unprotected sexual intercourse and STI, and in improving the quality of sexual relationships. Secondary objectives relate to the wider effects on school ethos, particularly on the status and implementation of sex education in schools, and on relationships between staff and students.

4. Trial design

RIPPLE is an open, stratified, cluster randomised controlled trial with extensive process evaluation as well as outcome evaluation. Intervention occurs at ages 13-14 years. In Phase 1 of the trial, students are followed-up to age 15-16; in Phase 2 follow-up of both arms is extended to ages 19 –20.

- 1. **Follow-up**

In Phase I, the first follow-up is conducted 6 months post-intervention at ages 14-15; and the second follow-up is conducted 18 months post-intervention at ages 15-16. At each follow-up information is collected by pen and paper questionnaire completed in the classroom setting. For pupils absent on the day of the survey, a questionnaire is left with the contact teacher and each absentee is invited to complete the questionnaire as soon as they return to school.

In Phase II , the third follow-up is conducted in the community at ages 17-18; the fourth and final follow-up is conducted in the community at ages 19-20. At this stage, follow-up information is collected through 1) anonymised linkage to statutory abortion and birth notifications, 2) postal questionnaire and 3) postal saliva or urine samples which will be tested for markers of STI exposure (see trial endpoints).

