**5 Plan of investigation**

**5.1 Trial register and assignment of ID codes**

The trial register is composed of all pupils enrolled in year 9 at the time of the baseline survey. Each pupil on the trial register is assigned a unique ID code, composed of 8 characters. The ID code consists of a two figure code for the school (01 to 28) a single digit for the Year 9 cohort (1 or 2) a three figure code for the pupil (001 to 900) and a check letter at the end.

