**5.2** **Survey Methods**

In phase I, questionnaire surveys are carried out in the classroom at baseline (pre-intervention), at 6 and 18 months post intervention for the two successive Year 9 cohorts. The questionnaires include measures of knowledge, attitudes, self-efficacy, sexual behaviour including vaginal intercourse, condom and contraceptive use, and views on any previous sex education. The questionnaires were developed and piloted in consultation with students, and include space for comments. Where possible, a member of the research team is present to explain the purpose of the questionnaire, reassure students about the confidential nature of their responses and answer any queries. In phase II, postal questionnaires, together with a urine or saliva “home testing kit” will be sent to all pupils on the trial register who give consent to be approached by the research team after they have left school.

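### Section 7.2 does not commit to using the baseline sexual behaviour that the trial collects when it analyses unprotected intercourse by age 16

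*Protocol*

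**What the plan says.** - **Endpoint.** Under Trial endpoints, Phase 1: "Primary endpoints are unprotected sexual intercourse before the age of 16 and regretted sexual relationships". Section 7.2 analyses the first of these as a probability by age 16. No start point is given.
- **Timing.** Section 4 (Trial design): "Intervention occurs at ages 13-14 years".
- **Baseline data.** Section 5.2: "questionnaire surveys are carried out in the classroom at baseline (pre-intervention), at 6 and 18 months post intervention". On content: "The questionnaires include measures of knowledge, attitudes, self-efficacy, sexual behaviour including vaginal intercourse, condom and contraceptive use". Table I shows the Year 9 baseline questionnaire as an activity in both arms.
- **Linkage.** Section 5.1: "Each pupil on the trial register is assigned a unique ID code".
- **Analysis.** In section 7.2 the GEE and multilevel comparisons carry no pupil covariates. Secondary versions adjust for "pupil level covariates: sex (first primary endpoint only), ethnic origin, social class etc". Section 7.1 compares events per person-year, unstratified and by the three randomisation strata, without saying when person-time starts.
- **Power.** Section 4.4: "over 90% power to detect a reduction in the proportion of pupils having unprotected intercourse before age 16, from 35% to 25"%, with a between-school standard deviation of 8.2%.

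**The concern.** A pupil's sexual experience at 13-14 is an obvious prognostic variable for unprotected intercourse by 16. A pupil who already has the event at baseline has the endpoint with certainty. The trial measures this before delivery and can link it to follow-up, yet section 7 gives it no stated role.

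Two things are at stake. First, with 14 schools per arm, chance differences between arms in baseline risk can be material, and an unadjusted comparison keeps whatever part the strata do not remove. The seven stratification factors in section 4.5 include no measure of pupils' sexual behaviour. Secondly, events before the intervention are counted although it cannot prevent them, so the contrast understates the relative effect among pupils still at risk.

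**Working it through.** **Inputs.** From sections 4.4 and 4.5: p0 = 0.35, p1 = 0.25, c = 14 schools per arm, m = 2 × 150 = 300 pupils per school, between-school SD 0.082, so k = 0.082/0.35 = 0.234. The 5% level is taken as two-sided. The documents give no baseline prevalence b and no share of between-school variance explained by baseline. Both are assumptions below, shown as ranges.

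**1. The plan's own figure.** SE² = [p0(1−p0)/m + p1(1−p1)/m + k²(p0² + p1²)]/c

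- Within-school part: 0.000758 + 0.000625 = 0.001383
- Between-school part: 0.006724 + 0.003431 = 0.010155
- SE = √(0.011538/14) = 0.0287, and 0.10/0.0287 = 3.48
- Power: 93.6% (normal) or 91.8% (t, 26 df)

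The stated figure of over 90% reproduces. The between-school part is 0.010155/0.011538 = 88% of the variance of a school mean.

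**2. Effect needed on later events.** Section 4.4 states 35% and 25% for the endpoint as defined, so both include earlier events. If a share b had the event at baseline in each arm, the ratio needed on later events is (0.25 − b)/(0.35 − b).

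| b (assumed) | Calculation | Ratio needed |
|---|---|---|
| 0 | 25/35 | 0.71 |
| 3% | 22/32 | 0.69 |
| 5% | 20/30 | 0.67 |
| 10% | 15/25 | 0.60 |

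The 10-point difference, and so the stated power, is unchanged.

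**3. Gain from the pupil-level value alone.** Since a baseline event implies the outcome, the variance it explains is R² = b(1 − 0.35)/[(1 − b) × 0.35]. This is 0.038 at b = 2% and 0.206 at b = 10%. Removing that share of the within-school part only:

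- b = 2%: SE 0.0286, power 93.7% (normal)
- b = 10%: SE 0.0284, power 94.1% (normal)

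Against 93.6%, the gain is at most about 0.5 point, because the within-school part is only 12% of the total.

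**4. Gain from school baseline prevalence.** Multiply the between-school part by (1 − g), leaving the within-school part alone and ignoring the degree of freedom that the covariate uses.

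| g (assumed) | SE | Power (t, 26 df) |
|---|---|---|
| 0 | 0.0287 | 91.8% |
| 10% | 0.0274 | 93.9% |
| 25% | 0.0254 | 96.7% |

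**5. Which school baseline is clean.** In Table I the cohort 1 baseline is Autumn 1997 and first delivery is Summer 1998. The cohort 2 baseline is Autumn 1998, in schools where the experimental arm has already delivered the programme. Section 3 itself expects wider effects on the school. Only the cohort 1 school prevalence is certain to precede any delivery.

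**The case against.** The covariate list is open-ended, and a separate analysis plan may settle covariates and event windows. This stands to the extent that the text supports only a failure to commit. A reader might infer that the baseline data go unused, which the protocol does not say.

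A reader might also infer that early events bias the result or cost power. Randomisation protects the comparison, since such events are expected equally in both arms. Power falls only if the ratio 25/35 is applied to later events alone: at b = 3%, 5% or 10% the difference would then be (35 − b) × 10/35 = 9.1, 8.6 or 7.1 points. Section 4.4 states its rates for the endpoint as defined, so that loss replaces the protocol's hypothesis with another one.

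Nor can between-school variance be called unexplained. Schools are ranked on seven risk factors and randomised within three strata, section 7.1 includes a stratified analysis, and section 4.4 notes that stratification can reduce k. What remains is that the strata do not contain pupils' own behaviour.

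Finally, section 7.1 leaves the start of person-time open, so the counting of early events is established only for the by-16 wording of section 7.2.

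**Conclusion.** The point holds as an available improvement that the protocol does not commit to. Baseline sexual behaviour is collected in both arms and linkable, yet it is absent from the main models and from the named secondary covariates. The stated power is sound without adjustment.

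The gain is removal of chance baseline imbalance plus modest precision. The pupil-level part is small whatever the baseline prevalence in the range tried. Any larger gain depends on how much between-school variance the school's baseline prevalence explains beyond the strata, which the documents do not show. Counting early events is a matter of interpretation and of how strong an effect the design presumes.

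The point is confined to the Phase I unprotected-intercourse endpoint. A reader might extend it to regretted relationships or termination, but section 5.2 does not list regretted relationships among the questionnaire measures, and termination comes from anonymised linkage, where a pupil-level covariate may not be available.

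**What to change.** 1. In the GEE and multilevel models for unprotected intercourse by age 16, adjust for the pupil's baseline sexual experience (ever intercourse: yes, no, missing) and for the school's prevalence at the cohort 1 baseline (Autumn 1997). Use that school value for both cohorts, not the cohort 2 school baseline.
2. Keep the ever-before-16 endpoint as primary. Redefining it to later events would change the estimand and is not needed.
3. Add an analysis restricted to pupils without the event at baseline. It will still include events between the autumn survey and the summer delivery.
4. In section 7.1, state when person-time starts, consistently with the events counted.

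No new data collection is needed. The cost is model wording, one added analysis and a rule for missing baseline answers. The unadjusted comparison can still be reported alongside.
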